### Project part II: assessment of the experience with the individualized VR-intervention

Aim, study design and setting: In a prospective clinical cohort study, we assess the influence of personalized VR videos on symptoms, well-being, and vegetative functionality. Data will be collected using questionnaires and patient record analysis. First and foremost, we want to ensure patient safety. Thus, the aim is to prove a non-inferiority of the intervention in this vulnerable group and to start with 10 patients at least. Further, we want to observe whether ceiling effects occur in terms of well-being in this patient group, and to match the subjective verbal judgment of the patients regarding well-being after the VR-experience compared to baseline to reflect on the assumption that the minimally clinically important difference for well-being as assessed with the MDBF (Multi Dimensional Well-being Questionnaire) [21] is a 0.5 standard deviation or actually more prior to the sample size calculation for a power of 0.8 with a one sided significance level of 0.05, resp. effect size in a consecutive larger sample [22, 23]. This piloting is important because from our assumption so far the sample size would range between 30 and 130 participants [24, 25].

Participants: The same inclusion and exclusion criteria apply as in project part I.

Intervention: We create personalized VR videos as requested from the patients, probably from the patient’s home or family members. After the videos are created, the patients watch the videos using VR headsets while being cared for in a hospital unit. The videos are edited to a length of about 3–15 min. The patients watch the generic nature video for comparison before or after the personalized video (1:1 randomization). Before and after watching the videos, the patients answer the questionnaires using a tablet computer; support by a trained research assistant is provided to the comfort of the patients. The whole procedure of VR application takes about 20–30 min. If desired, patients can watch the personalized video repeatedly on different days for a maximum duration of 14 days. If patients are interested, they will be provided with the video file.

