Questionnaires: Symptom perception (minimal documentation system, MIDOS) [26], well-being (MDBF Multidimensional Well-Being Questionnaire) [21], subjective benefit of VR videos (2 self-developed items), cybersickness (SSQ Simulator Sickness Questionnaire) [27], presence experience (SPES Spatial Presence Experience Scale) [28].

In addition to interviewing patients after viewing VR videos, information on disease, treatment adherence, pain medication, and vegetative functionality will be collected from patient records to avoid further, potentially burdensome physical examinations during study participation.

Data analysis: The analysis is performed with the total data set reflecting the intention-to-treat principle. Descriptive methods are used for the analysis of all collected data (frequency distributions, mean, median, interquartile). For the pre/post comparisons of the outcomes (well-being, symptom perception, treatment experience, treatment adherence, pain medication, autonomic functionality), with well-being as the primary outcome, non-parametric Wilcoxon signed-rank t-tests for repeated measures data are calculated. Analysis is performed using IBM SPSS Statistics and R (r-project.org).

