## Discussion

This study aims to investigate whether individual VR videos provide benefits in terms of symptom relief, well-being, treatment satisfaction, and treatment adherence in palliative cancer care. The novelty of this project are the individualized VR videos as in previous research with palliative patients only generic videos, such as nature shots, were used.

A further strength of the study is that the patients’ opinions as well as those of the relatives and the patient advisory board are considered, i.e., heavily involving those concerned by the intervention in its development. The combination of qualitative and quantitative method allows to inform the subsequent project parts: In the first part, we start with qualitative interviews to gain an in-depth understanding of the topic. We ask not only about wishes and needs, but also about worries and concerns. The results of the first part enable us to respond with a high degree of flexibility to the needs of the patients in the second part of the study. Moreover, we ensure patient safety when we assess and compare cybersickness, symptoms, and use of medication for symptoms before and after the intervention with no tolerance for a decline of the patient’s subjective wellbeing. The study is designed to implement VR video use tailored to the needs of patients feasible not only under laboratory conditions but in everyday clinical practice.

However, the generalisability of our study results will be limited because we perform a single centre study. Nevertheless, the experiences from the project may inform others who want to adapt the intervention to their site or to other palliative care samples. In terms of the sample, we suspect that particularly highly burdened patients will not participate in the study, although they would like to use the VR intervention outside of a trial. For this reason, we involve relatives and the patient representatives’ experiences and attitudes as a proxy. Whether older patients will be more likely to decline study participation because of restraints towards new technology is an apprehension that could not be clarified in former studies applying VR interventions to older people [29], and we aim to consider the particular needs of vulnerable and old people to operate the VR intervention.

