The NCT funding board reviewed a summary of this study to ensure its aims and objectives, study design and outcome are suited and promising to improve the care of cancer patients. The Institute for Biometrics of the Heidelberg University Hospital reviewed the quantitative data analysis plan and recommended descriptive methods. The anthropologist and research coordinator of the Department of Palliative Care of the Heidelberg University Hospital reviewed the protocol regarding the qualitative methodology and mixed methods approach. Further, three members of the NCT patient advisory board informed the interview guide, the selection of questionnaires, and the sheets for informed consent. They found it important to explore the potential of individualized VR-videos to alleviate the situation of palliative inpatients with cancer. In this context, they welcomed the approach to find out the wishes and concerns of patients and relatives related to the intervention to guide its implementation.

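### Part II sets out to prove non-inferiority from a step it calls piloting, yet its only test is a pre/post test of no change and the cited biometric review recommended descriptive methods

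*Protocol article*

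**What the plan says.** Three places in the protocol article bear on the status of the Part II data.

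- **Project part II, aim, study design and setting.** The aim follows from patient safety: "the aim is to prove a non-inferiority of the intervention in this vulnerable group and to start with 10 patients at least". This first step is also meant to look for ceiling effects and to check the assumption that the minimally important difference on the MDBF well-being questionnaire "is a 0.5 standard deviation or actually more". That check comes before a sample size calculation "for a power of 0.8 with a one sided significance level of 0.05" in a later, larger sample. The paragraph closes: "This piloting is important because from our assumption so far the sample size would range between 30 and 130 participants".
- **Project part II, data analysis.** Descriptive methods are planned for all collected data. In addition, for pre/post comparisons of six outcomes with well-being as primary, "non-parametric Wilcoxon signed-rank t-tests for repeated measures data are calculated". The analysis uses the total data set.
- **Discussion.** The Institute for Biometrics "reviewed the quantitative data analysis plan and recommended descriptive methods". Elsewhere the Discussion describes the safety assessment as made "with no tolerance for a decline" in subjective well-being. No numeric non-inferiority margin appears in the article.

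**The concern.** To prove non-inferiority is a confirmatory claim. It needs a margin and a test or interval that can exclude a decline larger than that margin, in a sample large enough to do so. Here the claim is attached to a pilot that precedes the sample size calculation, the named test has a different null hypothesis, and the reported advice was descriptive. These statements stand together in the published text, so the problem is not a detail that a fuller document would merely fill in.

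What is at stake is the safety conclusion in a vulnerable group. A reader who is told that the aim is to prove non-inferiority, and then sees a non-significant signed-rank test, could take that result as the proof. With about 10 patients, non-significance is likely even if well-being has really fallen by the amount the article itself assumes to be important.

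**Working it through.** **Inputs (Project part II, aim paragraph).** First sample n = 10, the stated minimum. Effect 0.5 SD on the MDBF. One-sided alpha 0.05 and power 0.8, both named for the later sample. Test: signed-rank, from the data analysis paragraph, which does not state sidedness.

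**Assumption.** The article does not say whether 0.5 SD refers to the raw scores or the change scores. The main calculation takes the SD of the change scores; step 3 shows the alternative.

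**1. The plan's own figure, 30 to 130.** For a paired comparison, n = ((z_alpha + z_power)/d)². With d = 0.5: ((1.645 + 0.842)/0.5)² = 24.7, so 25. The noncentral-t version gives 27, and dividing by the signed-rank efficiency 3/π gives 27/0.955 = 28.3, so 29. The lower end of 30 is consistent with the stated inputs. The upper end of 130 needs d = 2.487/√130 = 0.22, which is not stated, so that end cannot be reproduced. The point does not depend on it.

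**2. Power at n = 10, change-score SD.** The noncentrality is 0.5 × √10 = 1.58, with 9 degrees of freedom and a one-sided critical value of 1.833.

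| Test at 0.05 | One-sided | Two-sided |
|---|---|---|
| Paired t | 0.43 | 0.29 |
| Exact signed-rank (8,000 simulations, normal changes) | 0.38 | 0.29 |

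By symmetry, a one-sided test for harm would miss a true 0.5 SD decline with probability 1 − 0.43 = 0.57 to 1 − 0.38 = 0.62.

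**3. If 0.5 SD refers to the raw scores.** The effect on the change scale is 0.5/√(2(1 − r)), where r is the pre/post correlation. The article gives no r, so a range is shown (noncentral t, one-sided 0.05, n = 10).

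| r | Effect in change-score SD | Power |
|---|---|---|
| 0 | 0.354 | 0.27 |
| 0.3 | 0.423 | 0.34 |
| 0.5 | 0.500 | 0.43 |
| 0.7 | 0.645 | 0.60 |
| 0.8 | 0.791 | 0.75 |

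Power exceeds one half only when the pre/post correlation is high.

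**4. What 10 patients can exclude.** For a mean change, the one-sided 95% bound lies 1.833/√10 = 0.58 change-score SD below the estimate. If the observed mean change were exactly zero, a decline of 0.5 SD would not be excluded.

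**5. What the test can and cannot show.** The null hypothesis of the signed-rank test is no change. Non-significance leaves both benefit and harm open. A significant improvement would exclude a decline, but that is a superiority result. If zero tolerance for decline is read as a margin of zero, non-inferiority becomes that same superiority test. An intervention that leaves well-being truly unchanged would then pass a one-sided 0.05 test only about 5% of the time.

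**The case against.** The strongest reply is that the article already treats the first step as a pilot. It says so, places the sample size calculation afterwards, and reserves alpha and power for the later sample. The test paragraph refers to the total data set and nowhere ties p-values to the first 10 patients. On this view the power figure measures a sample that was never said to be powered. That stands in part: the figure does not show that a stated power was missed. It shows only that about 10 patients cannot carry a proof of safety. It also applies to the MDBF alone, because 0.5 SD is given for no other outcome. The reply does not explain why the word *prove* is attached to that same step.

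Three stronger readings are tempting, and the document supports none of them.

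- *The biometric advice was ignored.* It was not. The data analysis paragraph adopts descriptive methods for all collected data and adds tests to them.
- *The review advised against any testing.* The Discussion reports a recommendation of descriptive methods. It does not say only descriptive methods, and the review itself is not available.
- *Six outcomes are tested as co-equal confirmatory claims.* Well-being is named as the single primary outcome.

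Nor does any sentence say that p-values from the first sample are confirmatory. That this could be inferred follows from the stated aim, and it remains an inference. The absence of an exploratory label is not in itself a fault in a condensed article. The fault is that the stated aim points the other way.

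**Conclusion.** The point holds as an unreconciled conflict between the stated aim, the status of the step and the named test. As written, the aim of proving non-inferiority cannot be met at the pilot stage: there is no numeric margin, the signed-rank test is not a margin-based test, and about 10 patients give one-sided power of only 0.38 to 0.43 for a 0.5 SD change in well-being. This rests on n = 10 (the stated minimum, so more patients would raise it), on normally distributed changes, and on 0.5 SD referring to change scores. On the raw-score reading, paired-t power runs from 0.27 to 0.75 for correlations of 0 to 0.8 and stays below 0.8 throughout. The reported recommendation of descriptive methods supports the correction but is not what makes the aim unattainable. The weight is moderate: no design change is needed, but the wording governs what may be concluded about safety.

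**What to change.** **Pilot stage.** In the Part II aim, replace the intention to prove non-inferiority with one to describe change in well-being, symptoms and side-effects. In the data analysis paragraph, report estimates of change with 95% confidence intervals, and state that any signed-rank p-values from this stage are exploratory.

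**Larger sample.** Reserve confirmatory inference for well-being, the primary outcome, once the sample size has been calculated. If non-inferiority is kept there, state the margin on the MDBF scale and use a matching one-sided test or confidence interval. State also whether 0.5 SD refers to raw or change scores, since the sample size depends on it.

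**Cost.** For the pilot, a few sentences and the reporting of intervals, with no new data and no change of design. Keeping non-inferiority later also requires a justified margin and a sample size based on it. The downside is that the pilot can no longer be reported as proof of safety.

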## Data Availability

Model participant information sheet and consent form, interview guides, and examples from the input window for the outcome assessments can be provided on request from the corresponding author.

## List of abbreviations

PPI: Patient and-Public-Involvement
VR: Virtual Reality
